### Study Participants

Representatives from all stakeholder groups involved in the implementation of the Medly Program will be recruited for participation.

#### Patients

Patients can be enrolled into the Medly Program provided they (1) are 18 years or older, (2) have been diagnosed with HF and are followed by a cardiologist at the HF clinic, (3) can speak and read English (or have an informal caregiver who does) to adequately understand the text prompts in the Medly app, and (4) are able to comply with using Medly (eg, able to stand on the weight scale, able to answer symptom questions). As the Medly program is being implemented as part of the standard of care, there is no explicit exclusion criteria for participating in the program and its evaluation. The duration of program participation will be decided by patients and their treating cardiologist on an individual basis.

Upon enrollment into the Medly Program, patients will be presented with the option of answering questionnaires and participating in interviews related to the program evaluation. Patients will be asked to sign a written consent form before participating in the evaluation.

#### Program Staff

All members of the Medly Program staff will be asked to participate in semistructured interviews. These include clinicians providing care for patients with HF in the HF clinic (n=7), telehealth analyst (n=1), project manager (n=1), and members of the implementation team (n=2). These individuals will be asked to sign a consent form before their first interview.

### Data Collection and Analysis

#### Objective 1: Measuring the Impact of the Medly Program

##### Impact Indicators

The primary outcome for evaluating the impact of the Medly Program is the number of hospitalizations because of HF in the 6 months before versus the 6 months after enrollment. Secondary impact outcomes comparing 6-month to baseline values are described below.

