### Evaluation Objectives and Research Questions

#### Objective 1

The first objective is to evaluate the impact of the Medly Program on health service utilization, patient health outcomes, and their ability to self-care. Alerts sent to patients and clinicians will help identify periods of symptom exacerbation and volume overload. The impact of this is expected to permit earlier intervention for worsening conditions, thus avoiding trips to the emergency department (ED) and hospitalizations. For patients who are enrolled into the Medly Program on hospital discharge, the program is expected to reduce 30-day readmission rates. In addition, participation in the Medly Program is expected to improve patients’ ability to self-care, leading to improved clinical outcomes and QoL.

#### Objective 2

The second objective is to evaluate the degree to which the Medly Program was implemented as intended and to identify the contextual barriers and facilitators of implementation. This objective will answer the following questions:

To what extent did the HF clinic implement the Medly Program as intended?What contextual factors influence the implementation of the Medly Program?What adaptations were needed to implement and sustain the program within existing clinical workflows?

#### Objective 3

The third objective is to describe patient usage patterns to determine adherence and other behaviors in the Medly Program. This objective will answer the following questions:

To what degree do patients adhere to the Medly Program and how do adherence patterns change over time?What factors influence patient adherence?

#### Objective 4

The fourth objective is to evaluate the costs associated with the implementation of the TM program from the perspective of the health care system (ie, public payer), the hospital, and patients.

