##### Planned Analyses

The primary analyses will be paired Student *t* tests and Wilcoxon signed rank tests comparing baseline and 6-month values for all patient-level outcomes. For patients enrolled in the Medly Program on hospital discharge, the 30-day readmission rate will be compared with the readmission rate before the launch of the Medly Program, as determined using hospital administrative data. Secondary analyses aimed at determining the longitudinal impact of the Medly Program (ie, using outcome data from the additional time points), and the correlation of independent variables (eg, patient characteristics and adherence rates) with outcomes will be analyzed using general linear mixed model procedures. In addition, descriptive statistics will be produced for all variables collected, which may inform necessary subgroup analyses. All statistical analyses will be performed using the statistical software application SPSS (IBM Corporation, USA) [39].

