##### Power Consideration

We will aim to recruit at least 108 patients into the Medly Program at the HF clinic before analyses of patient-level outcomes are undertaken. This number is based on being able to detect a small effect size (Cohen *d*=0.3) in the number of hospitalizations because of HF within the first 6 months of enrollment with 80% power and an alpha of .05 (two-sided) [40]. This number considers that approximately 20% of patients will be “lost to follow-up,” which includes patient mortality and those who withdraw from the program before the 6-month time point. We anticipate recruiting this number in the first 18 months of the program.

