### Limitations

Unlike TM systems evaluated in the context of academic research, the lack of strict patient inclusion and exclusion criteria for the Medly Program has the potential to lead to heterogeneity among evaluation participants, which will make it difficult to generalize the results to other health care settings. Another important limitation is that the nature of this evaluation and the availability of data do not allow for a distinct comparator group. Without discounting these limitations, we believe that one of the strengths of this evaluation is its pragmatic nature and that these threats to internal and external validity will be mitigated through a detailed description of the context and participants when results are reported. The interpretation of the Medly Program evaluation results will include comparisons with previous TM RCTs conducted within the HF clinic [30] and other comparable settings, as well as other RCTs evaluating interventions designed to promote self-care through education and health coaching conducted within the HF clinic [51]. This is possible because of the selection of outcome metrics common in other TM studies.

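### The primary before/after count of HF hospitalizations does not exclude the admission from which discharge-enrolled patients enter, which biases the contrast toward benefit by an amount that depends on their share

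*Protocol article*

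**What the plan says.** Under Impact Indicators, the primary outcome is "the number of hospitalizations because of HF in the 6 months before versus the 6 months after enrollment". Planned Analyses for Objective 1 gives the test: "The primary analyses will be paired Student *t* tests and Wilcoxon signed rank tests comparing baseline and 6-month values".

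The article states in two places that some patients enter at discharge. Objective 1 says "For patients who are enrolled into the Medly Program on hospital discharge, the program is expected to reduce 30-day readmission rates", and Planned Analyses says "For patients enrolled in the Medly Program on hospital discharge, the 30-day readmission rate will be compared with the readmission rate before the launch". That 30-day readmission comparison is the only analysis in which this group is handled separately. Eligibility neither requires nor rules out a recent admission: under Patients, "there is no explicit exclusion criteria for participating in the program and its evaluation".

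Limitations concedes that "the availability of data do not allow for a distinct comparator group" and says that "these threats to internal and external validity will be mitigated through a detailed description of the context and participants". It also plans to interpret the results against earlier randomized trials, including trials run in the same clinic. It mentions neither the enrolling admission nor regression to the mean.

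**The concern.** In a paired before/after comparison, the two windows must have the same chance of containing an event when the intervention does nothing. That fails for anyone who enters because an event has just happened. A patient discharged from an HF admission and enrolled that day has that admission in the before window with certainty, while an admission in the after window occurs only at the background rate. Pooling these patients with clinic-enrolled patients adds their share directly to the mean difference.

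The primary conclusion of Objective 1 is at stake, because a fall in HF admissions could be partly or wholly an artefact of how the baseline is counted. Days in hospital (a secondary outcome) and the public payer costs under Objective 4, which include hospitalizations, use the same before/after contrast and inherit the same excess.

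**Working it through.** **The plan's own figure.** Power Consideration gives d = 0.3, 80% power, two-sided alpha 0.05, about 20% loss and a target of 108.
- Normal formula: ((1.96 + 0.84)/0.3)² gives 88 after rounding up; 88/0.8 = 110.
- Paired t test (noncentral t): 90; 90 × 1.2 = 108, which matches the plan.
- Dividing by the retained fraction instead gives 90/0.8 = 112.5, or 113. This is a small difference and not the point here.
- Completers at 20% loss: 108 × 0.8 = 86.4, taken as 86. Power at d = 0.3 is then about 78.5%.

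**Inputs that the article does not give (assumptions).**
- f: the share of patients enrolled on discharge from an HF admission. Varied.
- λ: background HF admissions per patient per 6 months. The Background section says that half of patients with HF are readmitted within a year, with no cause stated. Treated as an HF rate with constant hazard, λ = −ln(0.5)/2 = 0.347, or about 0.35. Varied from 0.1 to 1.0.

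**Model with no program effect.** Before = Poisson(λ) + Bernoulli(f); after = Poisson(λ). Then
- mean difference = f
- variance of the difference = 2λ + f(1 − f)
- spurious d = f / √(2λ + f(1 − f))
- apparent reduction = f / (λ + f)

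At λ = 0.347 and 86 completers (rejection from 4,000 simulated paired t tests):

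| f | spurious d | apparent reduction | rejection |
|---|---|---|---|
| 10% | 0.1/√0.783 = 0.113 | 0.1/0.447 = 22% | 18% |
| 20% | 0.2/√0.853 = 0.217 | 0.2/0.547 = 37% | 51% |
| 30% | 0.3/√0.903 = 0.316 | 0.3/0.647 = 46% | 83% |

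Letting rates differ between patients (gamma frailty, λ = 0.35) barely changes the rejection rates: 18%, 52% and 83% by t test, and 19%, 52% and 84% by Wilcoxon.

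**Share at which the artefact equals d = 0.3.** Setting the spurious d to 0.3 gives 1.09f² − 0.09f − 0.18λ = 0, so f = [0.09 + √(0.0081 + 0.7848λ)]/2.18.

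| λ | 0.1 | 0.2 | 0.35 | 0.5 | 0.75 | 1.0 |
|---|---|---|---|---|---|---|
| f needed | 18% | 23% | 28% | 33% | 40% | 45% |

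**Sensitivity to the base rate at f = 30%.** Rejection is about 94%, 82%, 71% and 46% for λ = 0.2, 0.35, 0.5 and 1.0. At f = 10%, d stays between 0.07 and 0.19 over λ = 0.1 to 1.0.

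**With the enrolling admission removed.** The mean difference is zero under this model. Simulated false findings of benefit occur 2.4% to 3.3% of the time, against a nominal 2.5% in that direction. The target of 108 does not change.

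**The case against.** **Silence is not a counting rule.** The article gives the windows but does not say how the enrolling admission is treated, and a fuller document may do so. It would be too strong to say that the plan expressly counts it. But the definition read literally does include it, and the article separates discharge-enrolled patients for one outcome without doing so for the primary one.

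**Not every patient is affected.** A reader might infer that the whole cohort carries a built-in before event. The eligibility criteria ask for a diagnosis and follow-up at the clinic, not an admission. The mechanism covers only patients discharged from an HF admission, and the article does not say how many there are. It also says nothing about clinic patients being referred when unstable, so no such effect is claimed or calculated here.

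**A significant fall is not guaranteed.** A reader might infer that the primary test would be expected to reject whatever the program does. At a 10% share it rejects only about 18% of the time. The result is also model-dependent: if discharged patients have twice the background rate after discharge (assumed 0.70 against 0.35, before rate unchanged), false findings of benefit fall to about 9%, 27% and 48% at shares of 10%, 20% and 30%. The bias shrinks but remains.

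**The authors acknowledge the design limit.** They call the missing comparator important, plan to read the results against randomized trials, and allow for subgroup analyses. That deserves credit. None of it changes the within-patient difference that the primary test uses.

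**Conclusion.** The point stands in conditional form. As written, the primary contrast does not exclude the enrolling admission, so it is biased toward benefit whenever some patients enter on discharge from an HF admission. The mitigation under Limitations does not remove that excess. At 0.35 HF admissions per 6 months, no program effect and 86 completers, false rejection is about 18%, 51% and 83% at shares of 10%, 20% and 30%. The artefact equals the whole planned effect at a share of about 28%, or 18% to 45% across base rates of 0.1 to 1.0.

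The direction follows from the definitions. The size rests on two assumed quantities, the discharge share and the base rate, and on equal background rates before and after. The figures measure only the built-in event; wider regression to the mean is not quantified. The documents do not support saying that the study can yield no conclusion about impact, because the problem lies in how the baseline is counted and most of it can be corrected in the analysis.

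**What to change.** 1. In the primary analysis, exclude the enrolling admission and its days from the before count, and apply the same rule to payer cost. Keep the unadjusted contrast as a sensitivity analysis.
2. Report the primary result separately for discharge-enrolled and clinic-enrolled patients, and state how many enter by each route.
3. Add a sensitivity analysis that omits patients first diagnosed at the enrolling admission. Removing that admission leaves them a before count of zero by construction, which reverses the bias. In the extreme case where all discharge-enrolled patients are of this kind (30% share, rate 0.35), a program with no effect would look significantly harmful about 23% of the time.
4. As support only, compare the after window with months −12 to −7 from the EMR, in patients diagnosed at least 12 months before enrolment. That block covers the same calendar months and lies away from the enrolment trigger. It should not be a required condition: it shrinks the sample, has an uncalculated power cost, reflects an earlier stage of disease, and may predate care at this hospital.
5. State in advance that a reduction which disappears once the enrolling admission is excluded will not be attributed to the program.

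Items 1 and 2 use data already planned, since utilization comes from the EMR and discharge-enrolled patients must be identified for the readmission comparison. Item 3 needs the date of diagnosis, and item 4 needs one further EMR extraction. The cost is a less favourable headline reduction and a little more analysis. Regression to the mean from enrolling patients during a period of worsening may remain and should be named under Limitations.

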###### Health Service Utilization

The number of hospitalizations (all-cause), 30-day readmission rate, days in hospital (HF and all-cause), number of ED visits (HF and all-cause), visits to family doctor (HF and all-cause), number of HF–related outpatient visits, and changes to medication will be recorded.

###### Left Ventricular Fraction and Laboratory Tests

The following HF–specific clinical parameters will be collected: left ventricular ejection fraction (LVEF), brain natriuretic peptide (BNP), creatinine, sodium, potassium, hemoglobin, and uric acid levels.

###### Mortality and Prediction of Survival

Patient mortality will be tracked. In addition, the Seattle Heart Failure Model (SHFM) will be calculated at program entry. Projected SHFM survival versus actual survival will be compared [33]. The calculation of this score requires data on age, gender, New York Heart Association classification, weight, LVEF, systolic blood pressure, list of medications (including diuretics), laboratory results (hemoglobin, lymphocytes, uric acid, total cholesterol, and sodium), and QRS interval.

###### Dyspnea

Patients will be asked to describe their level of breathlessness using a visual analogue scale for dyspnea on a scale ranging from 0 (no shortness of breath) to 10 (shortness of breath is the worst it can be).

###### Quality of Life

The EQ-5D-5L is a measure of generic health status and will be administered to all patients as a measure of QoL [34,35]. This 5-item instrument has undergone validity and reliability testing for several conditions including HF. Due to the generic nature of this measure, it is recommended that it be administered along with supplementary measurements to capture more disease-specific aspects related to QoL. Hence, the Minnesota Living with Heart Failure Questionnaire (MLHFQ) will also be administered. The questionnaire contains 21 items scored on a 5-point Likert scale, the responses of which are summed to produce a total score and subscores for the domains of physical and emotional QoL. The MLHFQ is widely used in studies involving HF–related QoL and has been shown to have a high level of reliability and validity [36].

###### Self-Care

The self-care of HF index asks respondents to respond to 22 items on a 4-point Likert scale to assess their ability to self-care across 3 subscales (maintenance, management, and confidence). The tool has undergone validity and reliability testing involving patients with HF [37].

###### Demographic Variables

Demographic information will also be collected using a questionnaire, which includes questions on the following: age, sex, income, native language, living arrangements (living alone, with a partner, or other), whether or not they have a caregiver (formal or informal), and type of living areas (eg, urban, suburban, or rural). In addition, patient comorbidities will be tracked. Finally, questions will be asked to assess the patient’s experience and comfort level with technology and smartphones, including frequency of use.

##### Data Acquisition

Data collection will occur at baseline, 1 month, 6 months, 12 months, and 24 months, or until the patient exits the program. Data collected in addition to the primary evaluation period (baseline to 6 months) will provide an opportunity for post-hoc analyses aimed at quality improvement, including recommended duration of use. For example, the 1-month time point was included to determine if the bulk of changes to self-care and QoL occur immediately after enrollment. Similarly, longitudinal data will help determine whether patient-level impacts are sustained or change when using the system long term.

Health service utilization, laboratory results, mortality, prediction of survival, and select demographic information will be obtained from the hospital EMR. In addition, health service utilization information will be verified by patient participants through self-reports via a questionnaire.

Baseline and follow-up questionnaires containing the validated survey tools listed in Table 1 will be distributed to patients during regularly scheduled visits. Upon study enrollment, patients will be asked whether they prefer to be mailed the questionnaire or completing it using an online survey tool (SurveyMonkey [38]) in the event that they do not have a clinic visit scheduled for the data collection time point. In these situations, the questionnaires will be sent to the patient according to the preferred format and they will be given 2 weeks to respond, after which a member of the evaluation team will call the patient to remind them to complete the questionnaire.

**Table 1 table1:** Timing of outcome assessments for the impact evaluation.

Domain and measure		Baseline	1 month	6 months	12 months	24 months	Exit

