#### Objective 2: Implementation Evaluation

The mixed-methods implementation evaluation will be guided by the framework by Proctor et al, which describes outcomes that can serve as indicators of implementation success [41], and the Consolidated Framework for Implementation Research (CFIR). The CFIR describes factors influencing implementation success according to 5 domains: (1) intervention characteristics, (2) outer setting, (3) inner setting, (4) characteristics of individuals, and (5) process [42].

**Table 2 table2:** Implementation outcome indicators.

Implementation outcome	Definitions^a^	Indicator
Adoption	The intention, initial decision, or action to try or employ an innovation or evidence-based practice. Adoption may also be referred to as “uptake”	Number of clinicians having decided to use Medly to monitor patients
Implementation cost	The cost impact of the implementation effort	See objective 4 for cost outcomes associated with implementation of the Medly Program
Feasibility	The extent to which a new treatment, or an innovation, can be successfully used or carried out within a given agency or setting	Number of patients enrolled; rate of patient enrollment; number of patient-initiated dropouts from the program; number of physician-initiated dropouts from the program—or no uptake
Fidelity	The degree to which an intervention was implemented as it was prescribed in the original protocol or as it was intended by the program developers	Number and nature of calls or emails made to the telehealth analyst; proportion of the number of—alerts acknowledged over the total number of alerts, phone calls to patients over the total number of alerts triggered, and false or inappropriate alerts over the total alerts triggered
Penetration	The integration of a practice within a service setting and its subsystems	Percentage of clinicians using Medly over the total number of potential clinician users in the HF clinic

^a^Definitions are based on the definitions provided by Proctor et al [41].

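### Data collection stops at an individually decided program exit, so the 12- and 24-month data cannot show what follows stopping and may be biased, in an unknown direction, on whether impacts last

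*Protocol article*

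**What the plan says.** Four parts of the protocol article bear on this.

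- **When collection stops.** Objective 1, Data Acquisition: "Data collection will occur at baseline, 1 month, 6 months, 12 months, and 24 months, or until the patient exits the program".
- **Who sets that date.** Study Participants, Patients: "The duration of program participation will be decided by patients and their treating cardiologist on an individual basis". Table 2 counts both kinds of exit separately, "number of patient-initiated dropouts from the program; number of physician-initiated dropouts from the program", and the Power Consideration section includes death in the loss.
- **What the later data are for.** Data Acquisition names two uses: "post-hoc analyses aimed at quality improvement, including recommended duration of use", and the statement that "longitudinal data will help determine whether patient-level impacts are sustained or change when using the system long term".
- **How they will be analysed.** The Planned Analyses for Objective 1 assign the extra time points to secondary analyses with general linear mixed models.

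Table 1 has an Exit column. It is marked for every utilization item except 30-day readmission, and for blood work, dyspnea, SCHFI, EQ-5D-5L and MLHFQ. It is not marked for LVEF. No column follows Exit. Utilization, laboratory and mortality data come from the hospital EMR, and patients verify utilization by questionnaire.

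**The concern.** How long to use a program depends partly on what happens when people stop. The plan stops observing each patient at that moment. What remains is each patient's course up to exit, and contrasts between patients whose durations were decided individually, quite possibly in response to how they were doing. There is no comparator group to separate the two. The Limitations section acknowledges the missing comparator and the heterogeneity of participants, but not selection through exit.

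The question of lasting impact is affected less severely. If patients who are doing badly leave or die, later results flatter the program. If stable patients leave because they no longer need monitoring, later results understate it. The documents do not say which would dominate. At stake is a policy use, advice on duration and on long-term benefit, drawn from data whose selection cannot be checked afterwards.

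**Working it through.** **1. The plan's own figure.** The only sample size given is 108, for the 6-month comparison. Inputs from Power Consideration: d = 0.3, power 80%, two-sided alpha 0.05, loss about 20%.

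- Normal approximation, paired: n = ((1.960 + 0.842)/0.3)² = 87.2, so 88; 88/0.8 = 110.
- Exact noncentral t: n = 90; 90 × 1.2 = 108.

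The stated 108 is reproduced (110 is within 2 patients). It covers 6 months only. The documents give no retention figure for 12 or 24 months.

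**2. Retention after 6 months.** Assumption: loss q recurs every 6 months, with the document's 20% as central value and 10% to 30% as the range. Remaining = N(1 − q)^(months/6).

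| q per 6 months | Share at 12 / 24 months | From 108 | From the 166 enrolled by April 2018 |
|---|---|---|---|
| 10% | 81% / 66% | 87 / 71 | 134 / 109 |
| 20% | 64% / 41% | 69 / 44 | 106 / 68 |
| 30% | 49% / 24% | 53 / 26 | 81 / 40 |

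**3. How far selection alone could move the results.** Both illustrations let sicker patients leave and hold every patient's true level constant. Reversing the selection reverses the sign.

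*Continuous outcome.* Simulation with correlation between visits of 0.5 to 0.7, 20% exit per 6 months, and exit likelier in worse patients (log-odds 0.5 to 1.0 per SD):

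- Crude mean of those remaining: drifts by 0.09 to 0.29 SD at 12 months and 0.19 to 0.49 SD at 24 months, against a planned effect of 0.3.
- Within-patient change among those remaining: at most about 0.09 SD. The sign depends on whether exit follows the previous or the current value.
- With exit unrelated to the outcome, both are zero.

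*Admissions.* Assume 30% of patients are high-risk with exit risk e per 6 months, and the rest have (0.20 − 0.3e)/0.7, so that 20% leave overall in the first 6 months. Compare the mean rate after four 6-month periods with the starting mean.

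- Wide contrast (rates 1.0 and 0.2, e = 0.40, others 0.114): start 0.3 × 1.0 + 0.7 × 0.2 = 0.44. Remaining at 24 months: 0.3 × 0.60⁴ = 0.039 high-risk and 0.7 × 0.886⁴ = 0.431 others. Mean (0.039 × 1.0 + 0.431 × 0.2)/0.470 = 0.266, a fall of about 40%.
- Narrow contrast (rates 0.6 and 0.3, e = 0.30, others 0.157): start 0.39. Remaining: 0.072 and 0.353. Mean (0.072 × 0.6 + 0.353 × 0.3)/0.425 = 0.351, a fall of 10%.

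These are falls in a crude mean, which the article does not plan as its longitudinal estimate. In the same settings, within-patient change is essentially zero. A random-intercept model gives an apparent fall of about 25% instead of 40% in the wide contrast, and about the same as the crude mean in the narrow one. The planned model therefore reduces the largest distortions without removing them.

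**4. What no model supplies.** Table 1 schedules nothing after Exit, so no patient contributes an outcome after leaving the program. This holds even if exit is unrelated to health.

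**The case against.** The other side has real force.

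- **Leavers are not discarded.** Table 1 has an Exit assessment, and a likelihood-based mixed model uses all records before exit. A reader might infer from the collection rule that the 12- and 24-month results describe only those who stayed. The documents do not support that for the planned data and model. It is true only of the values observed at those visits.
- **Some off-program data exist.** The 6 months before enrollment are the stated comparator. Only outcomes after exit are missing.
- **The target may be users.** The question about lasting impact is worded for people using the system long term, and the article's 1-month example is a within-patient question that needs no data after exit. On-program data are relevant to both.
- **No faulty duration contrast is written down.** The article does not say it will compare patients with different durations. It only leaves little else on which a duration recommendation could rest.
- **The stakes are limited.** The duration analyses are labelled post hoc and the longitudinal analysis secondary. Withdrawal reasons are documented. Handling of informative exit in a secondary model is commonly left to a fuller plan that is not shown.

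All of this stands and narrows the point. It does not remove it. The stopping rule for data collection is stated in the article, and no later analysis plan can recover outcomes that were not collected. The model's protection requires that exit depend on recorded data. The Exit assessment helps with that for planned departures, but death and sudden deterioration are the cases where it is least assured.

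**Conclusion.** The point holds in a limited form. Tying collection to participation means that outcomes after stopping cannot be assessed. It also leaves the 12- and 24-month results open to bias from informative exit. If 20% loss recurs every 6 months, about 64% remain at 12 months and 41% at 24 (49% to 81% and 24% to 66% for 10% to 30% loss).

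The size of any bias cannot be derived from the documents. It is zero if exit is unrelated to outcome. In the illustrations it is largest for crude means and smaller for within-patient change. A mixed model is less affected than the crude mean where selection is strong, but not clearly so where it is weak.

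A reader might also infer that longer use will falsely look beneficial. The documents do not fix that direction, because exit is a joint decision, can be initiated by either side, and could remove stable patients as well as sick ones. Nor does the point touch the 6-month primary comparison. It is a cheap improvement to a secondary analysis.

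**What to change.** **In Data Acquisition and Table 1:** continue EMR extraction of admissions, ED visits, days in hospital and mortality to 24 months from enrollment for every consenting participant, whatever the exit date. Questionnaires can still end at exit.

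**In Planned Analyses:**

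- Analyse 12- and 24-month utilization in all enrollees, accounting for death, with on-program results as secondary.
- Describe utilization rates before and after exit by documented exit reason, using EMR-recorded events on both sides so that like is compared with like.
- State that no recommended duration will be based on comparing patients whose durations were individually chosen.

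If follow-up cannot be extended, withdraw the duration aim and name selection through exit under Limitations.

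**Cost:** a longer extraction from a source already in use, and consent wording to cover it. No added visits or questionnaires. The drawback is that care at other hospitals after exit would be missed, because verification by patient self-report ends at exit.
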